### Randomization

A postal survey on baseline characteristics will be sent to potential participants. Respondents to this first survey will be randomly allocated to the intervention and the control group. Randomization will be conducted by a statistician of the Institute of Social Medicine and Epidemiology, University of Lübeck, who is not otherwise involved with the trial, by using computer-generated random numbers. Allocation will be stratified by a pension insurance agency.

### Sample size estimation

To detect a 10-point higher rate of applications for a medical rehabilitation program (controls: 50 %), 1,076 persons (538 per group) are needed relying on a 2-sided alpha error of 0.05 and a power of 0.90. Response rates of 30 % to the first survey and of 50 % to the second survey were assumed to calculate the gross sample size to be drawn from the insurance registers. We finally decided to draw 8,000 persons for both the federal agency and the two regional agencies to allow segmented analyses according to the type of agency. Sample drawing was stratified by sex and the duration of sickness benefits in the year prior to the first survey (15 to 30 days versus more than 30 days).

### Data management

The insurance agencies generate numeric pseudonyms as unique identification numbers for all randomly selected individuals. The insurance agencies will post the pseudonymized questionnaires to the sampled individuals. Persons will be informed that in case of participating in the first survey they will be randomly allocated either to the intervention or the control condition. Participants will then send back their questionnaires to the researchers. After the first survey is completed, random assignment will be performed, and participants will obtain their corresponding intervention letter. Intervention letters for both the participants of the control group (see Additional file 1) and the intervention group (see Additional file 2) are available for more details. One year later, a second survey will be conducted. Moreover, the insurance agencies will provide administrative data on rehabilitation events to the researchers if participants give their approval. The numeric identification numbers will be used by the researchers to match questionnaire and administrative data. Consequently, researchers’ access to personal data of the sampled individuals (e.g. addresses and insurance account numbers) is avoided. Additionally, access and utilization of the webpage will be documented during the study period and provided as aggregated data by the open analytics platform Piwik (http://piwik.org).

## Outcome measures

### Main study outcome

The primary outcomes are the proportion of applied and utilized medical rehabilitation services after 1 year in the intervention group as compared to the control group. These data will be extracted from the individual GPI accounts.

### Secondary outcome

Secondary outcomes will be assessed by questionnaire after 1 year. These outcomes include cognitions on rehabilitation and the application process as well as indicators of work ability, health-related quality of life and perceived disability. Further secondary outcomes are days with sick leave benefits and days of regular employment during the 1-year follow-up. These data will be also extracted from the individual GPI accounts.

#### Attitudes toward medical rehabilitation and application of rehabilitation

Attitudes toward medical rehabilitation and the application process which will be assessed are related to positive and negative outcome expectancies, perceived self-efficacy to manage an application and self-rated level of information.

Positive outcome expectancies, e.g. managing work demands after the rehabilitation, will be assessed by four 5-point scaled items (1 = “absolutely agree” to 5 = “absolutely disagree”). In addition, work-related and family-related negative outcome expectancies, e.g. fear to be seen by co-workers as a slacker and uncertainty about who will keep obligations at home, will be assessed each by three items. Perceived self-efficacy to manage an application, e.g. certainty to apply for a rehabilitation even if it is complicated, will be assessed by four 4-point scaled items (1 = “agree” to 4 = “do not agree”) following Schwarzer et al. [24]. Finally, the current level of information about the application process, e.g. to be well-informed which documents are needed for the rehabilitation application, will be assessed by four 4-point scaled items (1 = “agree” to 4 = “do not agree”).

#### Self-rated work ability and disability days

Self-rated work ability will be assessed by the Work Ability Score (WAS). This is the first item of the WAI and compares current self-rated work ability to the lifetime’s best. The item has an 11-point scale, where 0 represents complete incapacity to work and 10 represents lifetime best work ability. The WAS correlates highly with the overall WAI score [33, 40]. Additionally, we will ask for the number of days during the last 6 months the participants have been kept from their usual work and housework activities (disability days) [41].

#### Health-related quality of life

Health-related quality of life will be assessed with 3 subscales of the 36-item Short-Form Health Survey of the Medical Outcomes Study (SF-36; physical functioning scale, mental health index and general health perception scale). The values of the scales range from 0 to 100. Higher values represent better health-related quality of life [42].

#### Sick leave benefits and regular employment

Information about days of sick leave benefits and days of regular employment will be extracted from the individual GPI accounts.

### Statistical analysis

The proportions of applied and utilized medical rehabilitation services will be compared by Pearson’s chi-squared test. Effects on continuous outcomes will be tested by analyses of covariance; thereby the baseline scores will be considered as a covariate [43].

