### Participants

Persons aged 40 to 59 years with prior sick leave benefits and regular employment of at least 6 months in the year before the beginning of the study will be included. Exclusion criteria are the receipt of pension benefits and the receipt of medical or vocational rehabilitation services during the last 4 years. Samples are randomly drawn from the registers of three pension insurance agencies, i.e. the federal agency and two regional agencies. Sampling will be stratified by pension insurance agency, sex and duration of sick leave benefits.

Persons will be informed about purpose and intervention of the study, its duration and data protection. Participation in the study will be consented by answering the questionnaire of the initial survey. Consent for using administrative data of the participants will be obtained by signature on the informed consent form during the second survey.

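### The primary comparison is an unadjusted chi-squared test although allocation is stratified by agency and baseline data are held: a valid choice that gives up a little efficiency at no saving (minor)

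*Protocol article*

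**What the plan says.** On the primary outcomes, the Statistical analysis section of the protocol article reads: "The proportions of applied and utilized medical rehabilitation services will be compared by Pearson’s chi-squared test". It names no stratification factor and no covariate for this test. The sentence that follows does adjust, but only the continuous outcomes: "Effects on continuous outcomes will be tested by analyses of covariance; thereby the baseline scores will be considered as a covariate".

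The design uses more structure than the primary test does:

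- Randomization: "Allocation will be stratified by a pension insurance agency".
- Participants: "Sampling will be stratified by pension insurance agency, sex and duration of sick leave benefits". Sample size estimation gives the two benefit-duration classes as 15 to 30 days and more than 30 days.
- Randomization again: "A postal survey on baseline characteristics will be sent to potential participants". Only those who respond are randomised, so the baseline questionnaire precedes allocation.

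In the analysis, agency appears only through the separate analyses by type of agency announced under Sample size estimation.

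**The concern.** When randomisation balances the arms within strata and the stratum predicts the outcome, part of the outcome variation cannot contribute to the difference between arms. An unstratified test still counts that part as noise. Its type I error then falls below the nominal level and some power is lost. Separately, a test without covariates makes no use of baseline variables that predict applying.

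Both conditions are plausible here. The Intervention section reports slight differences between agencies in procedures and forms, and separate webpages for each. The behavioural model on which the guide is built treats outcome expectancies and self-efficacy as drivers of the intention to apply.

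What is at stake is precision, mainly if the true effect is smaller than planned. The Background section itself warns that web-based information does not necessarily lead to more decisions than in a control group.

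**Working it through.** **1. Reproduce the planned sample size.** Inputs from Sample size estimation: 50 % in controls, "To detect a 10-point higher rate of applications for a medical rehabilitation program" (hence 60 %), "relying on a 2-sided alpha error of 0.05 and a power of 0.90".

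n = [z(0.975)·√(2·p̄·(1−p̄)) + z(0.90)·√(p₁(1−p₁)+p₂(1−p₂))]² / d²

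= [1.960·√0.495 + 1.2816·√0.49]² / 0.01 = 518.04, so 519 per group.

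With the continuity correction, (n/4)·[1+√(1+4/(n·d))]² = 537.85, so 538 per group. This matches "1,076 persons (538 per group) are needed". The planned size is that of an unadjusted two-proportion test, so it agrees with the planned analysis and is not in error.

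**2. Expected numbers.** 16,000 × 0.30 × 0.50 = 2,400 analysable, or 1,200 per group. Within one agency type, 8,000 × 0.30 × 0.50 = 1,200, or 600 per group.

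**3. Stratifying by agency alone.** Assumptions: two equally large agency types, arms exactly balanced within each, and a gap g between the types in the application rate. With a pooled rate of 0.55, the share of outcome variance explained by agency is R² = (g/2)² / (0.55 × 0.45). Power and type I error come from 20,000 simulated trials at 538 per group, comparing Pearson's test with the Cochran-Mantel-Haenszel (CMH) test.

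| Agency gap | R² | Power, Pearson | Power, CMH | Type I error, Pearson | Type I error, CMH |
|---|---|---|---|---|---|
| 5 points | 0.003 | 0.912 | 0.913 | 0.046 | 0.046 |
| 10 points | 0.010 | 0.910 | 0.913 | 0.048 | 0.051 |
| 20 points | 0.040 | 0.917 | 0.922 | 0.041 | 0.048 |
| 30 points | 0.091 | 0.924 | 0.936 | 0.036 | 0.048 |

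As a check, the large-sample size of Pearson's test under the null (pooled rate 0.50, R² = (g/2)²/0.25) is 2·[1 − Φ(1.96/√(1−R²))]. This gives 0.049, 0.045 and 0.040 for gaps of 10, 20 and 30 points. The simulated values lie slightly lower because counts are discrete and because of simulation error (standard error √(0.05 × 0.95/20,000) = 0.0015). The pattern is the same: never above 0.05 in any material way, and lower as the gap widens.

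**4. Adding baseline covariates.** Adjustment is approximated by multiplying the variance of the difference by (1−R²), which is the same as analysing n/(1−R²). R² is assumed; the article gives none.

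| R² | Fall in standard error, 1−√(1−R²) | Power, 50 % vs 60 %, 538 per group | Power, 50 % vs 55 %, 1,200 per group |
|---|---|---|---|
| 0 | – | 0.910 | 0.689 |
| 0.05 | 2.5 % | 0.924 | 0.711 |
| 0.10 | 5.1 % | 0.936 | 0.734 |
| 0.20 | 10.6 % | 0.959 | 0.783 |

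The 5-point effect in the last column is also an assumption.

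**5. Unadjusted power for the planned 10-point effect.** It is 0.999 at 1,200 per group and 0.937 at 600 per group.

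**The case against.** The strongest case for leaving the plan alone is that nothing in it is wrong. Pearson's test is valid for two randomised proportions, it matches the sample size calculation exactly, and at the expected sample the planned effect will be detected almost surely with or without adjustment. All of this stands. So does the point that every gain shown rests on an agency gap, an R² or an effect size that the article does not supply, and that gaps of 5 or 10 points gain next to nothing.

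Three narrower objections also stand:

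- The conservatism is conditional. The Randomization section mentions computer-generated random numbers and strata, but no blocking. If assignment within agency is unrestricted, the arms need not be balanced there and Pearson's test has its nominal size. Sex and benefit duration are sampling strata, not allocation strata, so omitting them is no mismatch with the randomisation.
- Baseline collection of work ability, expectancies and self-efficacy is inferred from the use of baseline scores in the ANCOVAs. The sections on the survey speak only of baseline characteristics. Questionnaire covariates can also be missing, so adjustment needs a rule for that.
- Agency is not wholly ignored. Separate analyses by agency type are planned, and the federal segment contains a single agency, so the unstratified test omits no allocation stratum there.

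What the objections do not remove is that using the allocation stratum and data already in hand would cost nothing in data collection. Nor is the choice simply left to an unseen analysis plan: the article names the test, and adjusts for baseline in the very next sentence for the continuous outcomes only.

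**Conclusion.** The point holds as a minor, free improvement in efficiency. Agency alone is worth about 0 to 1 point of power at 538 per group over gaps of 5 to 30 points. Most of any gain would come from baseline covariates: 2 to 9 points of power for a 5-point effect at 1,200 per group (0.711 − 0.689 to 0.783 − 0.689) if they explain 5 to 20 % of the variation. For the planned effect at the expected sample the gain is negligible. The improvement would matter more for a smaller effect, or in the analyses by agency type.

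A reader might infer more, and the documents do not support it:

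- *That the standard errors are wrong or the test invalid.* At most the test is conservative, and only if arms are balanced within agency and agency predicts applying; the article establishes neither.
- *That adjustment would repair selection at the second survey, where consent for the administrative data is obtained.* Nothing in the article shows this. Adjustment would not help where response depends on unmeasured factors, on arm or on having applied.
- *That the lack of a stated effect measure or confidence interval is a fault.* A short analysis section in a journal article commonly leaves this to the full protocol or analysis plan, which is not shown.

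**What to change.** In the Statistical analysis section, before outcome data are seen, replace the primary test with one of the following:

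1. a Cochran-Mantel-Haenszel test stratified by pension insurance agency; or
2. a logistic regression with agency, sex, benefit-duration class and, if collected at baseline, self-rated work ability, with a simple stated rule for missing covariate values, reported as a standardised risk difference with 95 % confidence interval.

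Keep Pearson's chi-squared test as a sensitivity analysis, and add agency to the ANCOVA models. The sample size need not change.

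The cost is one or two sentences. The first option uses only agency, which is known for everyone randomised. The second needs no new data collection either, only the missing-covariate rule. Fixing the choice in advance matters, because adjustment introduced later could be read as data-driven.

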### Ethical approval

The study protocol was approved by the ethics committee of the Hannover Medical School, Hannover, Germany (Number: 2060-2013). The committee stated that there are no legal or ethical concerns to the planned procedures. The trial was registered in the German Clinical Trials Register on 16 January 2014 (Identifier: DRKS00005658).

## Discussion

Our randomized controlled trial will provide highest ranked evidence to clarify whether theory-driven web-based information supports access to rehabilitation services for people with prior sickness benefits.

## Trial status

Conception and development of the web-based information guide is finished. Recruiting has started and is ongoing.

## Abbreviations

FAQ: frequently asked questions
GPI: German Pension Insurance
HAPA: health action process approach
SF-36: 36-Item Short-Form Health Survey
WAI: Work Ability Index
WAS: Work Ability Score
